A list of eligible patients is generated each morning. Patients are then approached by one of the patient navigators in the waiting room of the prenatal clinic and offered an opportunity to participate in the study. If interested, informed consent is obtained and baseline data collected. This may take place in the waiting room, an examination room, or an educational office, when available. Patients randomized to the intervention arm then participate in a brief in-person educational session led by the patient navigator, whose experience includes teaching small undergraduate courses. The navigator’s training for the study included developing an understanding of the methods used to develop the quality measures, use of the MHQP website and obtaining informed consent. Both the primary and secondary navigators participated in extensive rehearsal of the intervention with the principal investigator (PI) feedback prior to piloting then enrolling patients. The information sessions include the rationale for quality measurement, how quality varies among practices, and that information about variation is publicly available. The information session is followed by in-person guided use of the MHQP website with the navigator. Each of two guided website sessions last approximately 20 minutes and take place at two prenatal visits. The first session takes place between 20 and 34 weeks gestation and the second 2 to 6 weeks after the first session. The navigator guides the participant in use of the MHQP website on a laptop computer. There is a standard explanation of the meaning of the quality performance measures and patientexperience survey data. The patient navigator provides the same demonstration to all participants about how the website can be used to assess a practice’s performance. Following this standard intervention, patients are shown performance data for practices they would like to view within a 25-mile radius of their home. If the participant does not have any practices she wishes to view, a standard set of three area practices with high and low scores are shown as examples. Practices shown are recorded. A copy of the study information pamphlet is given after the first guided website session and the participant is asked if they have questions about the pamphlet. During the second intervention session, the patient navigator asks if the participant had an opportunity to look at the website themselves. The navigator then invites them to look at local pediatric practice data again and will respond to any questions about performance data for these practices. Participants may complete a worksheet during the intervention in which they fill out a table of scores on performance measures for the practices they review. Patient navigators do not recommend one practice over another but do discuss the practices’ quality scores and what the scores mean. Objectives of the IDEAS for a healthy baby intervention are outlined in Table 2, along with methods to achieve objectives.

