### Outcome assessment

All enrolled patients will be interviewed after delivery, prior to hospital discharge for outcome assessment. This assessment will include the name of the pediatric practice where the newborn has a scheduled visit (required by Baystate prior to infant discharge) and follow-up measures outlined.

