### Measures

#### Primary outcome

The MHQP website uses a star system for rating practices on each of nine measures of pediatric clinical quality with a maximum of four stars. Similarly, the site uses a star system for rating practices on each of seven patient experience measures. A mean quality score and a mean patient experience score will be created for each practice within a 25-mile radius of the hospital that has data reported on the MHQP website for at least three relevant measures. The primary outcomes will be a) the mean MHQP clinical quality and b) mean patient experience scores of the pediatric practices selected by the participants in the navigator intervention compared to the control. All measures are summarized in Table 3.

**Table 3 T3:** Summary of outcome and other measures

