### Analysis

#### Intervention efficacy

Descriptive statistics will be used to characterize the study population and evaluate the distributions of outcomes, predictors and covariates. We will use *t*-tests and Wilcoxon rank-sum tests to compare mean quality and patient experience scores of the pediatric practices selected between women randomized to the navigator intervention and the information pamphlet control. This analysis will be both overall and within strata defined by parity (0, 1+). Our primary analysis will be intent-to-treat, based upon randomization, whether or not the intervention sessions occurred. Patients who choose practices that do not appear on the MHQP website will not be included in the primary outcome analysis but will be included in secondary outcome analyses. Secondary analysis will adjust for compliance with the intervention. We will also evaluate analysis of variance models for the mean quality and patient experience scores, adjusting for parity and any baseline patient characteristics that were not balanced between the intervention groups. An interaction effect for intervention with parity will be included to test for difference in the intervention efficacy between women selecting a pediatrician for the first time versus those with children. Confounding by covariates will be assessed. In addition we will explore the impact of clustering of women within neighborhoods defined by residential zip code, since location of practice relative to home may have a large impact on choice of practice. Final models will provide an estimate of the patient navigator effect on the quality and patient experience ratings of selected pediatric practice, both overall and by parity, adjusting for important maternal characteristics. If practice scores on the website should change during the course of the study, the scores present during the prenatal period will be used in the analysis.

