### Power/sample size

Power was evaluated to detect a difference between intervention groups in mean quality and patient experience ratings of pediatric practices, within strata defined by parity (0, 1+). In an 18-month period, we anticipate 2,250 pregnant women will be seen at the Wesson Women’s OB and Midwifery Clinic. Based upon prior experience with research recruitment in these clinics, we expect to be able to approach about two thirds, or approximately 1,500 women. Of these we anticipate 1,200 will meet age and language eligibility requirements and that 730 will agree to participate, with 650 completing baseline and post-delivery data collection.

Expecting approximately 40% nulliparous women [28], we will need to have at least 130 women in each study arm within strata defined by parity. Quality data were identified on the MHQP website for 18 practices within a 25-mile radius of Springfield, with a mean (SD) quality score of 3.1 (0.5) on nine pediatric measures. Mean (SD) patient experience scores were similar at 3.0 (0.6). Using a significance level of 0.01, we will have power greater than 80% to detect a mean difference of 0.2 units in quality scores between control and intervention, within each stratum of parity. Power is greater than 80% to detect a 0.25 difference in mean patient experience ratings. The magnitude of the differences (0.2, 0.25) would indicate a meaningful difference in mean quality or patient experience rating of practices selected, yet this difference is large enough that we expect it could be detected.

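### The primary analysis is labelled intent-to-treat but drops women by the practice they choose after randomization, so the arm comparison can be biased in either direction, by an unknown amount

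*Protocol article*

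**What the plan says.** In the protocol article, Analysis, Intervention efficacy, the analysis principle is: "Our primary analysis will be intent-to-treat, based upon randomization, whether or not the intervention sessions occurred". The sentence that follows it is: "Patients who choose practices that do not appear on the MHQP website will not be included in the primary outcome analysis". The excluded women are kept for secondary outcomes only.

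Under Measures, Primary outcome, the comparison is of the clinical quality scores and the "mean patient experience scores of the pediatric practices selected by the participants in the navigator intervention compared to the control". The same section creates a score only for a practice "within a 25-mile radius of the hospital that has data reported on the MHQP website for at least three relevant measures".

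The practice is recorded late (Outcome assessment): "All enrolled patients will be interviewed after delivery, prior to hospital discharge for outcome assessment". By then the sessions have taken place. In those sessions (IDEAS intervention), "patients are shown performance data for practices they would like to view within a 25-mile radius of their home", and a woman with no practice in mind is shown a standard set of three area practices. Controls receive the pamphlet alone.

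**The concern.** Whether a woman enters the primary analysis depends on which practice she picks. That pick follows randomization, generates the outcome, and is what the intervention tries to change. Guided use of the website could draw women towards listed practices, or could move a woman away from a poorly rated listed practice to one with no rating. The share excluded, and the kind of woman excluded, may therefore differ between arms. Equal shares would not settle the matter, because different women could be missing from each arm.

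The retained groups are then no longer the randomized groups. A difference in mean score could appear without anyone choosing a better-rated practice, or a real one could be masked. The planned t-tests and rank-sum tests cannot tell these cases apart. The adjustment for imbalanced baseline characteristics, the compliance analysis and the zip-code clustering do not address selection on the outcome itself.

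**Working it through.** **Inputs from the article.** Power/sample size gives a mean clinical quality of 3.1 and SD 0.5 over 18 practices, a target difference of 0.2, significance level 0.01, 650 completers, 40% nulliparous, and at least 130 per arm per parity stratum. Primary outcome gives a maximum of four stars.

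**Assumptions.** The article does not give the share choosing unscored practices, the scores of women who move, or a minimum score (1 is assumed). The figures in steps 2 to 5 are illustrations.

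**1. The plan's own figure.** 650 × 0.40 / 2 = 130, exactly the stated minimum. The standard error is 0.5 × √(2/130) = 0.0620, and 0.2 / 0.0620 = 3.225. Power is Φ(3.225 − 2.326) = 81.6% one-sided and Φ(3.225 − 2.576) = 74.2% two-sided. The stated power above 80% reproduces one-sided only; sidedness is not stated and is a separate matter. What matters here is that nothing is allowed for unscored choices. With 10% unscored, 117 per arm remain and power is 76.8% one-sided (68.6% two-sided). With 20%, 104 remain and power is 71.2% (62.1%).

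**2. Women leave listed practices.** Suppose every control is scored with mean 3.1, and a share p of navigated women leaves practices scoring 2.6 (one SD below the mean) for unlisted ones. The shift in the scored-only mean is (3.1 − p × 2.6)/(1 − p) − 3.1.
- p = 10%: 2.84/0.90 − 3.1 = +0.056, or 28% of the 0.2 target.
- p = 20%: 2.58/0.80 − 3.1 = +0.125, or about 62% of the target.

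**3. Women enter listed practices.** Suppose 20% of controls and 10% of navigated women choose unlisted practices, with no effect on anyone else.
- The diverted 10% choose practices scoring 3.6: (0.8 × 3.1 + 0.1 × 3.6)/0.9 − 3.1 = +0.056.
- They choose practices scoring 2.6: (0.8 × 3.1 + 0.1 × 2.6)/0.9 − 3.1 = −0.056.
- With 30% against 10% unlisted, the shift is ±0.111.

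The sign depends on where the diverted women go, which is not known.

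**4. Effect on error rate.** A bias of 0.05 would raise a two-sided 0.01 test to about 3.9% at 130 per arm (0.05/0.0620 = 0.806 standard errors) and about 9.7% at 325 per arm.

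**5. Does assigning the area mean repair it?** Give each unscored practice 3.1 in both arms.
- Leave, 10%: 3.1 − 0.26 + 0.31 = 3.15, a shift of +0.050 against +0.056 (90% remains).
- Leave, 20%: 3.1 − 0.52 + 0.62 = 3.20, a shift of +0.100 against +0.125 (80% remains).
- Enter, 3.6: 0.8 × 3.1 + 0.1 × 3.6 + 0.1 × 3.1 = 3.15, a shift of +0.050 against +0.056 (90% remains).

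One constant does not solve the problem. Varying the value shows how far the answer depends on it. In the 10% leave case the difference is 0.1v − 0.26 when unscored practices are given v. That is zero at v = 2.6, +0.05 at 3.1, and runs from −0.16 at v = 1 to +0.14 at v = 4. With a fraction e unscored in each arm and scores from 1 to 4, the bounds on the arm difference are 2 × 3 × e wide: 0.30 at 5% and 0.60 at 10%.

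**6. Two definitions of unscored.** Intervention efficacy excludes women whose practice is not on the website. Primary outcome gives no score to a listed practice that is more than 25 miles from the hospital or reports fewer than three measures. A woman choosing such a practice is not excluded by the first section but has no score under the second. She could have been shown that practice, because the viewing radius is measured from her home.

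**The case against.** An unlisted practice has no website score, so some convention is unavoidable. This is an undefined outcome handled by complete cases, and no measured values are being discarded. The article also says what it means by intent-to-treat: analysis by assigned arm whether or not sessions were attended. No woman changes arm, and the exclusion is stated openly. All of that stands, and it limits the charge to a loose label and an unprotected analysis set.

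The sizes are assumed. The leave scenario needs 10 to 20% of navigated women to abandon low-scoring practices specifically for unlisted ones, although navigators recommend no practice. In the enter scenario at 3.6, a woman guided to a well-rated practice arguably shows an intended effect. The 3.1 is a mean over practices, not over women's choices. If unlisted choices are rare, the distortion is negligible. These points stand too.

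An analysis plan that is not shown may contain sensitivity analyses, and their absence from the article is no fault. But the article itself fixes the primary analysis set and its name, and that is the point here.

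**Conclusion.** The point holds in this form: the primary comparison is restricted to women with a scored practice, that restriction depends on a choice made after randomization which the intervention targets, and the result should not be called intent-to-treat without qualification. It can be biased in either direction, for both primary outcomes.

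The size is unknown. Under the assumed movements of 10 to 20% of women, the clinical quality mean shifts by about 0.06 to 0.13 against the 0.2 target. This rests on a score gap of 0.5 and on shares that the article does not state.

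A reader might infer that the trial will overstate the navigator's benefit. The documents do not support that: they give neither the unlisted share nor any difference between arms, and the same arithmetic yields negative shifts. A reader might also infer that assigning the area mean to unscored practices would restore an intent-to-treat analysis. Step 5 shows that it would not.

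**What to change.** - Describe the current primary comparison as one among women who chose a scored practice, and drop the intent-to-treat label for it.
- Report and compare by arm the proportion choosing a scored practice, as an outcome to be read together with the two mean scores.
- Prespecify an analysis of all randomized women with a known practice. Vary the value given to unscored practices from the lowest to the highest area score, separately by arm, as a tipping-point or bounds analysis. Claim benefit only if the conclusion holds over a plausible range stated in advance.
- Do not make single-value imputation at the area mean the primary analysis.
- Use one definition of an unscored practice in Primary outcome and Intervention efficacy, covering website listing, distance from the hospital and the minimum of three measures.

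The practice name is already collected at the post-delivery interview, so no new data are needed. The cost is revised wording and a few extra runs. If many choices prove unscored, the conclusion may be less definite. The article reports enrolment as still under way, so the change can be made before the arms are compared.

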### Recruitment and informed consent

Women will be given a one-page study fact sheet by office staff when they first present to the Wesson Women’s Clinic. When women check in for their prenatal visit during weeks 20 to 34 of gestation, they will be reminded of the study by one of the two trained patient navigators and will be given the one-page fact sheet again as a reminder of study goals. If a woman expresses interest in enrolling, informed consent will then be obtained. Baseline data will be collected and the patient will be randomly assigned to the navigator intervention or the pamphlet control. Randomization will be stratified based on parity because women who have already selected a pediatric practice for their older children may be less likely to change practices based on quality performance alone. If randomized to the intervention arm, the first intervention session will ensue. If in the control arm, the patient will be given an informational pamphlet (described below). If the study process is interrupted, it will be continued at subsequent prenatal visits or by phone when feasible. A flow diagram for the study is shown in Figure 1.

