#### Other measures

**Demographics** Demographic data collected will include age, race/ethnicity, country of birth, parity, household income, marital status, number of adults in the household, number of children in the household, insurance status, primary language spoken at home, and name of current pediatric practice if the participant has children.

**Use of publicly reported data** As part of the study survey, we will determine participants’ familiarity with health care quality measures, variation in quality of care, awareness of publicly reported health care quality data, and their personal use of publicly reported health care quality data outside of the study.

**Health literacy and numeracy** The Newest Vital Sign (NVS) is a screening tool that assesses general literacy and numeracy skills as applied to health information. Individuals examine information on a nutrition label and answer six questions about how they would interpret and act on that information. The NVS takes approximately 3 minutes to complete.

**Challenges encountered using website data to guide provider choice** At the post-delivery interview, women will be asked what difficulties, if any, they encountered acting upon the information they accessed either with the navigator or on their own using the information pamphlet. Anticipated barriers include limitations imposed by the participant’s insurance carrier and transportation difficulties.

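### Apart from parity, covariates for the adjusted models are picked by observed imbalance and an undefined confounding check, when they should be fixed in advance on prognostic grounds

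*Protocol article*

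**What the plan says.** The Intervention efficacy section first compares the arms by t-tests and Wilcoxon rank-sum tests, overall and by parity. It adds: "Our primary analysis will be intent-to-treat, based upon randomization, whether or not the intervention sessions occurred". No covariate is named for that comparison.

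The adjusted analysis comes next: "We will also evaluate analysis of variance models for the mean quality and patient experience scores". The rule for choosing the covariates in these models is stated as "adjusting for parity and any baseline patient characteristics that were not balanced between the intervention groups". A further sentence states: "Confounding by covariates will be assessed". The product is described as follows: "Final models will provide an estimate of the patient navigator effect on the quality and patient experience ratings of selected pediatric practice". It is to be given overall and within parity groups, and the covariates are there described only as "adjusting for important maternal characteristics".

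Parity is the one covariate fixed in advance for these models, and the plan gives a reason. Under Recruitment and informed consent, "Randomization will be stratified based on parity", because mothers who already have a practice may be less inclined to switch. The pool of other candidates is wide. Under Other measures, "Demographic data collected will include age, race/ethnicity, country of birth, parity, household income, marital status, number of adults in the household", with further household, insurance and language items and the Newest Vital Sign (NVS). Table 3 adds baseline activation scores and awareness and use of quality data. I count about 12 to 15 candidates besides parity.

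**The concern.** Adjustment in a randomized trial pays off when the covariates predict the outcome. A difference between randomized arms at baseline arises by chance and carries no information on that. A rule keyed to imbalance can admit a variable unrelated to the score of the chosen practice and leave out a strong predictor that happens to be balanced. The confounding check is a second step decided on the trial data. Analysts who have seen the data by arm could defend several different final models, each with its own estimate.

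At stake are the precision of the adjusted navigator effect and its independence from choices made after the data are seen. This is not a complaint about detail left to an analysis plan. The protocol states the selection rule, and an analysis plan that followed it would inherit the weakness.

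**Working it through.** **Inputs from the Power/sample size section.** SD 0.5 for clinical quality and 0.6 for patient experience; differences 0.2 and 0.25; alpha 0.01, sidedness not stated; 650 completers, 40% nulliparous, so 650 × 0.40 / 2 = 130 per arm in the smaller stratum and 650 × 0.60 / 2 = 195 in the larger.

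**The plan's own figure.** Power = Φ(δ / (SD × √(2/n)) − z).
- Quality at n = 130: standard error 0.5 × √(2/130) = 0.0620, and 0.2 / 0.0620 = 3.225. One-sided (z = 2.326): Φ(0.899) = 81.6%. Two-sided (z = 2.576): Φ(0.649) = 74.2%.
- Patient experience: 84.9% one-sided, 78.3% two-sided.

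The stated power above 80% is thus reproduced with a one-sided alpha of 0.01. Sidedness is a separate matter. The two-sided value is used below as the unadjusted reference.

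**How often chance supplies a covariate.** Assume a 5% test for imbalance and k independent characteristics; the plan names neither. P(at least one flagged) = 1 − 0.95^k, which is 34% for k = 8, 46% for k = 12 and 54% for k = 15. This shows that entry to the model is largely a matter of chance. It does not measure harm.

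**What a fixed prognostic set could gain.** Adjustment multiplies the standard error by √(1 − R²). For quality at 130 per arm:
- R² = 0.1: 3.225 / 0.949 = 3.399; Φ(3.399 − 2.576) = 79%
- R² = 0.3: 3.225 / 0.837 = 3.854; Φ(1.278) = 90%
- R² = 0.5: 3.225 / 0.707 = 4.561; Φ(1.985) = 98%

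**Simulation of the rules.** Assumptions: 12 independent baseline covariates, 3 of them prognostic with the joint R² shown; unbalanced means p < 0.05; a confounder is a variable that moves the estimate by more than 10%. Power at 130 per arm, difference 0.2, SD 0.5, two-sided alpha 0.01, 2,000 runs (Monte Carlo error about 1 percentage point):

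| R² | Unadjusted | Imbalance rule | Confounding check alone | Fixed prognostic set |
|---|---|---|---|---|
| 0.1 | 74% | 74% | 76% | 78% |
| 0.3 | 73% | 74% | 83% | 89% |
| 0.5 | 74% | 75% | 91% | 97% |

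The imbalance rule performs like no adjustment. A change-in-estimate check recovers part of the gain, but the plan gives no criterion for its check.

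**Type I error.** No effect, 325 per arm, 4,000 runs, nominal two-sided 1%: the imbalance rule rejected in 1.1%, 0.6% and 0.5% of trials at R² 0.1, 0.3 and 0.5. Taking the smallest p-value among the unadjusted, imbalance-adjusted and confounding-adjusted results gave 1.2 to 1.4%, and 6.4 to 7.0% at a nominal 5%.

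**The case against.** Several points on the other side stand.

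- **The primary result is not exposed.** The adjusted models are introduced as an addition to the t-test and Wilcoxon comparison, so the primary comparison appears to be unadjusted. A reader might infer that the main result depends on covariate selection; the text does not support that.
- **Prognosis is not ignored altogether.** Parity enters whatever the balance and for a prognostic reason. The criticism applies only to the other covariates.
- **Validity is not broken.** A reader might infer that selecting on imbalance makes the nominal standard error too small. The simulation shows no inflation, and conservatism when covariates are prognostic. Picking the smallest of three p-values would inflate error modestly, but nothing in the plan proposes that.
- **The loss is a forgone gain.** The power statement claims no benefit from covariates, and the documents supply no R². At R² = 0.1 the difference is about 4 points. With 195 per arm the unadjusted two-sided power for quality is already 91.5%, and with 325 per arm 99.4%, so there the benefit is mainly a narrower interval.
- **Not all imbalance in the analysed set need be chance.** Women who choose practices absent from the website are left out of the primary outcome analysis, and 730 enrolled become 650 completers. Because practice choice is what the intervention targets, this exclusion could differ by arm. That is a fair reason to examine the analysed set, but as a sensitivity analysis and not as a screen that determines the final model.

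**Conclusion.** The concern holds for the supplementary adjusted models. Their covariates other than parity are chosen by a rule unrelated to prognosis and by a check without a criterion, yet these models supply the adjusted navigator effect overall and by parity. The cost is lost precision and freedom to choose a model after seeing the data. It is not inflated type I error from the imbalance rule, and it does not compromise the primary comparison.

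The size depends on how well baseline characteristics predict the score of the chosen practice. At 130 per arm, over an assumed R² of 0.1 to 0.5, a fixed set gives about 78% to 97% power against 74 to 75% under the imbalance rule. The upper end should be read with care. The most obvious predictor, the score of the current practice, exists only for women with children, whereas 130 per arm is the size of the nulliparous stratum. The simulation also assumes independent covariates and a 5% imbalance test. The direction of the result does not depend on a particular R², as long as some named covariates are prognostic.

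**What to change.** Before data are examined by arm (the Trial status section says enrolment is under way), replace the imbalance rule and the confounding check with a covariate set chosen on prognostic grounds and used whatever the observed balance. An example, for the sponsor to settle: parity, age, race/ethnicity, NVS score and, for women with children, the MHQP score of their current practice.

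Only the name of the current practice is collected, so its score must be derived. It does not exist for nulliparous women, and it will be missing where the practice lies outside the 25-mile radius or has fewer than three reported measures. State that it enters within the parous stratum, or with a missing/not-applicable indicator in the overall model.

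Show baseline balance descriptively. Keep any check for imbalance caused by leaving out women who chose unlisted practices, but label it a sensitivity analysis and do not let it select the final model.

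The cost is a short rewrite of the section, a little work to derive the current-practice score, and a few degrees of freedom. No new data collection is needed.

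### Home location, which the plan thinks may strongly shape the choice of practice, is only explored as zip-code clustering and is not prespecified as a baseline predictor: a loss of efficiency, not of validity

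*Protocol article*

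**What the plan says.** Randomisation is by woman. Under Recruitment and informed consent: "Baseline data will be collected and the patient will be randomly assigned to the navigator intervention or the pamphlet control". The only stratification factor is parity: "Randomization will be stratified based on parity because women who have already selected a pediatric practice".

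Under Analysis, Intervention efficacy, the committed comparison is unadjusted, using "tests and Wilcoxon rank-sum tests to compare mean quality and patient experience scores of the pediatric practices selected between women randomized" to the two arms, overall and by parity. Analysis of variance models follow, "adjusting for parity and any baseline patient characteristics that were not balanced between the intervention groups". Location then enters in one sentence: "we will explore the impact of clustering of women within neighborhoods defined by residential zip code", and the reason given is that "location of practice relative to home may have a large impact on choice of practice". The paragraph ends with final models that adjust for maternal characteristics judged important, which are not listed.

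The article names no method for the clustering step (random effect, fixed effect, robust variance or design effect). It names no distance or area covariate.

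**The concern.** The reason and the remedy do not match. If where a woman lives helps to determine which practice she picks, location may predict the score of that practice. A variable known before randomisation that predicts the outcome belongs in the mean model, where it removes variation from the arm comparison. Clustering corrections answer a different problem, which arises when whole neighbourhoods are allocated to one arm.

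The covariate rule does not fill the gap, because it selects on observed imbalance and not on prognostic strength. A strongly predictive location variable that happens to be balanced would stay out under that rule, although it would still improve precision.

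Precision is at stake for both primary scores, chiefly among nulliparous women. They form the smaller stratum, and they have no current pediatric practice that could serve as a baseline predictor instead.

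**Working it through.** **Inputs from Power/sample size.** Significance level 0.01, sidedness not stated. 650 completers with about 40% nulliparous gives 650 × 0.40 / 2 = 130 per arm, and 650 × 0.60 / 2 = 195 per arm in the other stratum. Clinical quality: SD 0.5, difference 0.2. Patient experience: SD 0.6, difference 0.25.

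**Assumed, not in the article.** The share of outcome variance explained by location (R²), and the number of zip-code areas.

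**Step 1: the plan's own figure.** Power = Φ(δ / (σ√(2/n)) − z).

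- Clinical quality: 0.2 / (0.5 × √(2/130)) = 3.225. Two-sided: Φ(3.225 − 2.576) = 74.2%. One-sided: Φ(3.225 − 2.326) = 81.6%.
- Patient experience: 0.25 / (0.6 × √(2/130)) = 3.359. Two-sided: 78.3%. One-sided: 84.9%.

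The stated power above 80% is reproduced one-sided only. The steps below use two-sided 0.01 unless noted.

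**Step 2: does zip-code similarity invalidate the t-test?** Simulation: 260 women, 20 assumed zip areas, individual 1:1 allocation, 4,000 runs per setting, zip code explaining 0 to 30% of variance. With no treatment effect the plain t-test rejected in 0.95% to 1.1% of runs, against a nominal 1%. No correction is needed.

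**Step 3: what could the unstated clustering method do?** Same simulation with a true difference of 0.2. Entries are power.

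| Variance explained by zip code | t-test | Zip fixed effects | Zip random intercept | Cluster-robust, unadjusted difference |
|---|---|---|---|---|
| 0% | 74% | 69% | 74% | 64% |
| 10% | 73% | 76% | 77% | 66% |
| 20% | 75% | 82% | 83% | 67% |
| 30% | 74% | 87% | 87% | 67% |

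The random-intercept column uses the true variance ratio, so it is slightly favourable. The cluster-robust loss comes mainly from the few areas: on 20 − 1 = 19 degrees of freedom the critical value is 2.861 instead of 2.576, and Φ(3.225 − 2.861) = 64%.

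A second simulation assumed 12 zip codes explaining 20% of variance. A cluster-robust z-test without small-sample correction rejected 4.0% under no effect. With correction it rejected 1.6%, and power was 61% against 74% for the t-test.

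**Step 4: gain from a location term in the mean model.** Replace σ by σ√(1 − R²). For clinical quality at R² = 0.10: 3.225 / √0.90 = 3.399, and Φ(3.399 − 2.576) = 79.5%.

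| R² of the location term (assumed) | 0 | 5% | 10% | 20% |
|---|---|---|---|---|
| Clinical quality, 130 per arm | 74.2% | 76.8% | 79.5% | 84.8% |
| Patient experience, 130 per arm | 78.3% | 80.8% | 83.3% | 88.1% |
| Clinical quality, 195 per arm | 91.5% | 93.0% | 94.4% | 96.7% |

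If the test is one-sided, the first row becomes 81.6, 83.7, 85.8 and 90.0% (2.326 in place of 2.576). Two-sided power of 80% at 130 per arm needs R² of about 0.11 for clinical quality and 0.03 for patient experience.

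**Step 5: form of the term.** R² in Step 4 is what the chosen term itself captures. In a further simulation a single location covariate left power at 74% when location explained nothing, and gained about 2 to 5 points when location explained 10 to 20%. Step 4 gives +2.6 points at 5% and +5.3 at 10%, so this matches a covariate that captures about half of the location signal. Zip fixed effects lost power when location explained nothing: 72.6% to 70.6% with 12 codes, and 73.7% to 69.1% with 20.

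**The case against.** A reader might infer that the clustering step can only distort the standard error. The article does not support that. No method is named, and the sentence sits between the analysis of variance models and the final models, so it can be read as a zip-code effect in those models. A zip random or fixed effect uses location as a predictor and captures the gain (Step 3). The harm from a cluster-robust variance arises only under a method the article does not mention. Naming the method is also the kind of detail a condensed article may leave to fuller documents.

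A reader might also infer that the plan firmly expects location to be decisive. The wording is hedged, and it concerns the choice of practice, not its score: a nearby practice may score high or low. A distance-decay model of choice gave median explained variance of 1% to 16%, so the 20% and 30% settings are optimistic.

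Three further objections stand. The committed t-test is valid as it is. The final models leave room for location among the unlisted maternal characteristics. Replacing the exploration with many zip-code factors would lose power if location explains little; break-even was roughly 5% to 8% explained variance.

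These objections limit the point but do not remove it. The article gives a prognostic reason for looking at location, commits only to exploring clustering, and fixes a covariate rule based on imbalance. A single covariate or a random intercept avoids the loss that many fixed effects risk.

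**Conclusion.** The point holds as a matter of efficiency. Nothing in the stated primary comparison is invalid, and an individually randomised comparison needs no correction for zip-code similarity. What the plan may lose is precision in the adjusted estimate. For clinical quality in the nulliparous stratum the gain is about 3, 5 or 11 power points if the location term captures 5, 10 or 20% of variance, and essentially nothing if location is not prognostic. In the 1+ stratum, where power is already 91.5%, it is about 1.5 to 5 points. These figures rest on two-sided 0.01, the plan's SDs and differences, and assumed explained variances. Because the clustering method is open, the planned step may capture this gain or cost power, so the text should settle which.

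**What to change.** Replace the clustering sentence with a commitment along these lines:

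> The adjusted model for each score includes arm, parity and a home-location term defined from the residential zip code at enrolment. No cluster-robust variance or design effect is applied to the arm comparison.

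Use a form with few degrees of freedom: one covariate, such as the mean score of the scored practices nearest her home, computed separately for clinical quality and patient experience; or a zip-code random intercept. Avoid many zip fixed effects. Define the covariate from information available before randomisation, and include it whether or not it is balanced. The planned arm-by-parity interaction and the t-tests can stay as they are.

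The cost is one or a few degrees of freedom and slight extra work linking zip codes to practices. The planned exploration already requires zip code, so no new data collection is involved.
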